### Secondary objectives

To estimate the impact of the TTM-based SMS messages (text 4 change) on regulating the level of biomarkers for cardiovascular and metabolic risks, lowering the indices of general and central obesity, and maintaining body measurements among nonobese individuals. To estimate the impact of the intervention program on the incidence of myocardial infarction, stroke, death and hospitalization. To examine the acceptability of the text 4 change motivational SMS messages among the intervention group.

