### Inclusion criteria

The inclusion criteria for participants is Saudi adults aged ≥18 years, literate, prediabetic, with no contraindication of physical activity, have a smartphone with easy access to the internet and are willing and able to provide written informed consent to participate in the study.

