### Exclusion criteria

The exclusion criteria for participants is pregnancy, individuals who do physical exercise > 50 min/week, follow a diet regimen, have a history of myocardial infarction, have impaired renal function, and are diabetic.

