### Healthy weight and anthropometric measurements

Participants will be classified according to WHO cutoff values for body mass index (BMI). Normal weight, overweight, obese and morbidly obese categories have a BMI of 18.5–24.9 kg/m^2^, 25–29.9 kg/m^2^, 30–34.9 kg/m^2^ and ≥ 35 kg/m^2^, respectively [41].

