### Study outcomes

By the end of the trial, we expect the following outcomes:

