#### Secondary outcomes at 6-month follow-up visits

Change in the TTM towards stages of action and maintenance, decreased levels of LDL-C to < 130 mg/dl or ≤ 5.1 mmol/l, change in the systolic\diastolic blood pressure to normal blood pressure < 120/80 mmHg, respectively, decrease in body weight by 5–10% per year, improvement in the physical activity level to the recommended 150 min per week and improvement in the daily consumption of portions of fruit and vegetables to 5–7 servings/day.

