### Data analysis plan

Data will be analyzed using the Statistical Package for Social Studies (SPSS 22; IBM Corp., New York, NY, USA). Continuous variables will be expressed as mean ± standard deviation or median and interquartile ranges according to the normality assessment. Categorical variables will be expressed as frequencies and percentages.

The chi-square statistical test will be applied for categorical variables to assess the association between them. The t-test or Mann-Whitney test will be used to compare numeric variables. Repeated measures analysis of variances or Friedman’s test will be used to evaluate repeated measures over the follow-up period.

The incidence rate and cumulative incidence rate will be computed for incidence of T2DM among the intervention and control groups. Additionally, comparison between the incidence of T2DM among different age groups and gender will be evaluated. Kaplan-Meier survival curves and log-rank tests will be used to compare the intervention and control groups as well as the different risk groups for progression to T2DM, and transition and/or relapses from different stages of TTM.

Hazards ratios with 95% confidence intervals will be calculated and the adjustment of known confounders will be adopted in the Cox regression model. In all the analyses, *P*-values < 0.05 will be considered statistically significant.

The principal analyses of primary and secondary outcomes will use the intent-to-treat approach. The intent-to-treat analyses will include all participants in their randomly assigned treatment groups regardless of a participant’s adherence to the assigned treatment regimen.

All data entry will be anonymous and identification numbers will be saved in a password-protected log file with the primary investigator. Backup of entered data will be created monthly to avoid any loss of collected data. An interim analysis of data will be conducted 12 months after recruitment of the last participants. Interim analysis aims to evaluate the completeness and accuracy of the collected data and early detection of any difficulties.

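### Blood pressure and LDL-C outcomes are fixed targets with no baseline restriction and no stated scale of analysis, the weight outcome conflicts with the nonobese objective, and no planned numeric test adjusts for baseline

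*Protocol article*

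**What the plan says.** The section on secondary outcomes at 6-month visits asks for "decreased levels of LDL-C to < 130 mg/dl or ≤ 5.1 mmol/l", for a change in systolic and diastolic blood pressure "to normal blood pressure < 120/80 mmHg, respectively, decrease in body weight by 5–10% per year", and for targets on stage of change, activity and fruit and vegetable intake. None of these is restricted by the participant's status at entry. The Study outcomes section introduces the list with "By the end of the trial, we expect the following outcomes".

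The Secondary objectives section aims to regulate cardiovascular and metabolic biomarkers and lower obesity indices. It adds "maintaining body measurements among nonobese individuals".

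Entry requires "Saudi adults aged ≥18 years, literate, prediabetic, with no contraindication of physical activity", plus a smartphone and consent. The exclusions include "individuals who do physical exercise > 50 min/week, follow a diet regimen" but no limit on blood pressure, LDL-C, weight or BMI. The anthropometry section opens its BMI classes with "Normal weight, overweight, obese and morbidly obese categories have a BMI of 18.5–24.9" kg/m², and lists overweight (25–29.9) separately from obese (30 and above).

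The Data analysis plan assigns tests by type of variable. "The chi-square statistical test will be applied for categorical variables to assess the association between them"; numeric variables get a t-test or Mann-Whitney test; repeated measures get repeated-measures ANOVA or Friedman's test. Primary and secondary outcomes are analysed by intention to treat. Covariate adjustment is mentioned only for the Cox model. The Physical measurements section has weight, blood pressure, HbA1c and lipids taken at baseline in all participants.

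**The concern.** There are three linked weaknesses.

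- **Scale of analysis.** Blood pressure and LDL-C are written as moves to a cut-off, while the test list would serve either a numeric value or a yes/no variable. The choice affects power. If it is yes/no, the treatment of people already at target also matters, and the text does not settle it.
- **Weight.** A nonobese participant whose weight stays stable meets the objective and fails the outcome. The trial could report the intended result in that subgroup as a failure.
- **Baseline.** The trial measures these variables at entry on everyone, but none of the numeric tests named conditions on that value. Precision that costs nothing is left unused.

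At stake is the ability to detect a true effect on the cardiometabolic measures, which the Abstract gives as the trial's other objective.

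**Working it through.** **1. Weight: objective against outcome.** The objective for nonobese participants is maintenance. The outcome for all is a loss of 5–10% per year. Normal-weight people can enter, and the trial lasts three years. Compounding gives 1 − 0.95³ = 14% and 1 − 0.90³ = 27%. For an assumed example with BMI 22, the end values are 22 × 0.857 = 18.9 and 22 × 0.729 = 16.0. The second lies below the article's own normal range of 18.5–24.9. No assumption about analysis is needed to see that the two statements disagree.

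**2. Who can already be at target.** For physical activity the target is 150 min/week and anyone exercising more than 50 min/week is excluded, so nobody should be at target at entry. Blood pressure and LDL-C have no such safeguard. For weight the question does not arise, because a percentage loss is itself a change from baseline.

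**3. Numeric comparison, with and without baseline.** The article states no power for a secondary outcome, so there is no figure to reproduce. Its 256 and 300 concern diabetes incidence. Assumptions, none from the article: systolic SD 14 mmHg, correlation r = 0.6, true difference 4 mmHg, two-sided 0.05. From the Sample size calculation section: 150 per arm, or 150 × 0.8 = 120 after 20% loss.

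Power = Φ(4 / (s·√(2/n)) − 1.96), where s is
- follow-up value: 14
- change score: 14·√(2(1 − 0.6)) = 12.52
- analysis of covariance: 14·√(1 − 0.6²) = 11.2

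| Method | n = 150: SE, ratio, power | n = 120: SE, ratio, power |
|---|---|---|
| t-test on follow-up | 1.617, 2.474, 70% | 1.807, 2.213, 60% |
| Change score | 1.446, 2.766, 79% | 1.617, 2.474, 70% |
| ANCOVA | 1.293, 3.093, 87% | 1.446, 2.766, 79% |

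**4. The same effect as systolic below 120, in everyone.** Control proportion Φ((120 − μ)/14), intervention Φ((124 − μ)/14), with the control mean μ assumed unchanged from baseline. Power = Φ[(|p₂ − p₁|√n − 1.96√(2p̄(1 − p̄))) / √(p₁(1 − p₁) + p₂(1 − p₂))].

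| Mean μ | Control | Intervention | Power, n = 150 | Power, n = 120 |
|---|---|---|---|---|
| 115 | 0.640 | 0.740 | 47% | 39% |
| 120 | 0.500 | 0.612 | 50% | 42% |
| 125 | 0.360 | 0.472 | 50% | 41% |
| 130 | 0.238 | 0.334 | 46% | 38% |

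This models the systolic limit alone, not 120/80 jointly.

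**5. How people already at target are scored.** Assume 128 per arm (the article's minimum) and that 20% against 35% of those not at target reach it. Power by share already at target:

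| Share at target | Counted as successes | Counted as non-successes | Left out |
|---|---|---|---|
| 0% | 77% | 77% | 77% |
| 20% | 49% | 64% | 67% |
| 40% | 31% | 49% | 55% |
| 60% | 18% | 33% | 40% |

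The first column is the proportion at target at the visit, with those at target staying there: at 40%, 0.4 + 0.6 × 0.20 = 0.52 against 0.4 + 0.6 × 0.35 = 0.61.

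**The case against.** The strongest reply is that the article announces no responder analysis. The list is introduced as what the investigators expect, the HbA1c entry among the primary outcomes is worded as an expectation too, and t-tests and repeated-measures ANOVA are planned for numeric variables. On that reading the cut-offs are hoped-for results and the loss in steps 4 and 5 never arises. This stands. A reader might infer that blood pressure, LDL-C and weight will be tested by chi-square as reached or not reached, with people already at target counted as successes. The text says neither. Someone already normal has arguably not changed to normal, so even that scoring is open.

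A second reply is that repeated-measures ANOVA with baseline as a time point does use baseline, and that choosing a covariance model is normally left to the analysis plan, which is not shown. The first half is right: with two time points the group-by-time test is the change-score test, at 79% rather than 70% in the illustration. It still falls short of the 87% from conditioning on baseline. The second half makes this a recommended improvement to the tests the article names, not an error in them.

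Third, the power figures rest on assumed inputs. The Abstract also speaks of recruiting 1016 people. With 508 per arm, step 3 gives at least 99% by any of the three methods, and the gain from adjustment would matter only for smaller effects.

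None of this touches the weight conflict, which is a disagreement between two statements in the same document.

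**Conclusion.** The point holds in three parts of different strength.

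- **Weight: firm.** The outcome and the objective for nonobese participants disagree and must be reconciled. A reader might describe this as scoring people who are already at target. That is not the problem, since nobody has lost 5–10% at entry.
- **Blood pressure and LDL-C: conditional.** The cut-offs carry no baseline restriction, people at target can enter, and the scale of analysis is not fixed. If attainment is compared in everyone, power falls from about 70–87% for the numeric methods to about 46–50% in the illustration at 150 per arm. If the values are compared numerically, that loss does not occur.
- **Baseline adjustment: an improvement under either reading.** It is worth about 17 points of power over a follow-up t-test and 8 over change scores at 150 per arm, and about 19 and 9 at 120 per arm.

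All power figures depend on SD 14, r = 0.6 and a 4 mmHg difference. A smaller r would shrink the gain over the follow-up t-test. The article claims no power for secondary outcomes, so no stated figure is shown to be wrong.

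**What to change.** 1. Define systolic pressure, diastolic pressure and LDL-C as the value at each visit, and weight as percent change from baseline. Compare arms by analysis of covariance, or by a mixed model over visits, adjusted for the baseline value.
2. Report attainment of the blood pressure and LDL-C targets as supportive only, among participants not at target at baseline.
3. Reconcile the weight outcome with the secondary objective, using the article's own BMI classes. Overweight participants are nonobese under those classes, so state which rule covers them and place each participant under one rule only. The choice of weight target belongs to the investigators.

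The cost is wording in the outcomes and analysis sections. All the measurements are already scheduled, so no visit, test or sample size changes. The change should be made before anyone sees outcome data by arm.

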### Data analysis plan

Data will be analyzed using the Statistical Package for Social Studies (SPSS 22; IBM Corp., New York, NY, USA). Continuous variables will be expressed as mean ± standard deviation or median and interquartile ranges according to the normality assessment. Categorical variables will be expressed as frequencies and percentages.

The chi-square statistical test will be applied for categorical variables to assess the association between them. The t-test or Mann-Whitney test will be used to compare numeric variables. Repeated measures analysis of variances or Friedman’s test will be used to evaluate repeated measures over the follow-up period.

The incidence rate and cumulative incidence rate will be computed for incidence of T2DM among the intervention and control groups. Additionally, comparison between the incidence of T2DM among different age groups and gender will be evaluated. Kaplan-Meier survival curves and log-rank tests will be used to compare the intervention and control groups as well as the different risk groups for progression to T2DM, and transition and/or relapses from different stages of TTM.

Hazards ratios with 95% confidence intervals will be calculated and the adjustment of known confounders will be adopted in the Cox regression model. In all the analyses, *P*-values < 0.05 will be considered statistically significant.

The principal analyses of primary and secondary outcomes will use the intent-to-treat approach. The intent-to-treat analyses will include all participants in their randomly assigned treatment groups regardless of a participant’s adherence to the assigned treatment regimen.

All data entry will be anonymous and identification numbers will be saved in a password-protected log file with the primary investigator. Backup of entered data will be created monthly to avoid any loss of collected data. An interim analysis of data will be conducted 12 months after recruitment of the last participants. Interim analysis aims to evaluate the completeness and accuracy of the collected data and early detection of any difficulties.

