#### Assessment of interventions

All participants will complete the WHO STEPS instrument version 3.1 at the baseline visit and during each follow-up visit. This will assess behavioral risk factors including healthy diet, physical activity and the participants’ behavioral change(s) stage based on the TTM at the baseline visit and follow-up visits for progression in the stages of change.

Data about adherence to physical activity and healthy dietary intake recommendations will be recorded at every 6-monthly follow-up visit. Adherence will be self-reported every 6 months and scored as poor, moderate or good. Physical activity and dietary intake will be categorized as adherent or nonadherent for statistical analysis.

At every visit after the baseline visit, we will assess the mobile messages in the intervention group through a specially designed questionnaire. It will assess the user acceptability and satisfaction of the SMS messages program using a scoring system of 0–10. It will assess message content, frequency, clarity, effect on personal life (“degree of disturbance”), and personal views of the impact of these messages on lifestyle. The list of questions also includes the preferred time to receive messages and invites suggestions for improvement. A maximum total score of 10 denotes that the text messages were highly acceptable and satisfactory, while the lowest score of zero denotes that the text messages were the least acceptable and unsatisfactory.

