#### Primary outcome

Adoption of healthy lifestyle behaviors including healthy eating and physical activity practices complying with WHO recommendations. Incidence of T2DM, based on a change in HbA1c with an expected reduction of 1–2% at the end of the trial.

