### Sample size calculation

A sample size of 300 is required so that there are 150 participants each in the intervention and control groups. The sample size was calculated by using Stata® software version 15 (StataCorp, College Station, Texas, USA) with the assumptions that α = level of significance (0.05), β = Type II error (power of the study = 1- β = 80%). The hazard rate of diabetes development among the control group is 10% over the 2 years, the hazard rate of diabetes development among the intervention group is 7% over the 2 years (reduction of about 30%) and the minimum sample size required to reject the null hypothesis is 256 (128 in each group). With an expected loss of follow-up around 20%, the sample size was increased to 300 participants in total.

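### For the behaviour primary outcome, the only between-arm test named is a chi-square, which on observed end-of-trial status would use about 240 of 300 participants and none of the earlier reports

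*Protocol article*

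**What the plan says.** All references are to the protocol article.

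- **Primary outcome.** The first item is "Adoption of healthy lifestyle behaviors including healthy eating and physical activity practices complying with WHO recommendations". Study outcomes places the outcomes at the end of the trial. No instrument, cut-off or test is attached to this item.
- **Assessment of interventions.** "Adherence will be self-reported every 6 months and scored as poor, moderate or good". Then: "Physical activity and dietary intake will be categorized as adherent or nonadherent for statistical analysis". The sections on physical activity adherence and dietary adherence assign the grades to the two classes.
- **Data analysis plan, categorical data.** "The chi-square statistical test will be applied for categorical variables to assess the association between them". No visit is specified.
- **Data analysis plan, repeated measures.** Repeated measures ANOVA or Friedman's test "will be used to evaluate repeated measures over the follow-up period". Kaplan-Meier, log-rank and Cox methods are assigned to T2DM and to movement between stages of change, not to adherence.
- **Data analysis plan, analysis set.** "The intent-to-treat analyses will include all participants in their randomly assigned treatment groups", whatever their adherence to the assigned regimen.
- **Sample size calculation.** "With an expected loss of follow-up around 20%, the sample size was increased to 300 participants in total".
- **Randomization and blinding.** Participants know their allocation.

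**The concern.** The behaviour outcome is a repeated yes/no report, and a participant who has left cannot supply the final one. Among the named methods, only the chi-square compares two arms on a yes/no variable. Repeated measures ANOVA is built for continuous data. Friedman's test is within-subject, so it does not compare arms, and both need complete records in their standard form. The T2DM outcome is less exposed, because the time-to-event methods use each person up to the last contact.

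A chi-square on observed final status therefore discards people who left, together with the earlier reports that say something about why they left. Participants are unblinded, only one arm receives messages, and compliance is self-reported. It is plausible, though not stated anywhere, that staying in the trial relates to compliance differently in the two arms. A completer comparison would then show some adoption effect where there is none.

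**Working it through.** **1. Who enters the test.** Inputs: N = 300 (150 per arm) and about 20% loss, both from Sample size calculation.

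- Without a final status: 0.20 × 300 = 60.
- Available to a chi-square on observed final status: 300 − 60 = 240, or 120 per arm.

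The Abstract speaks of 1016 participants, so the larger case is 1016 / 2 = 508 per arm.

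**2. What the observed data alone can say.** With a fraction m = 0.20 missing in each arm, the difference over all randomised participants lies within (1 − m) × observed difference ± m. For an assumed observed 50% against 35%:

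- 0.8 × 15 = 12 points, so the range is 12 ± 20, from −8 to +32 points.

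These are worst-case limits, not an expected bias.

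**3. Illustrative simulations under the null.** The documents give no adherence or dropout pattern, so everything here except the arm sizes, the six visits and the 20% loss is assumed. Adherence is the same in both arms, with six follow-up visits, a participant-level random intercept with SD 2 on the logit scale, and about 20% loss per arm. In one arm only, the chance of leaving is 7% after a nonadherent report and 1% after an adherent one.

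| Simulation | Analysis | Mean false difference | Rejection, 150 per arm | Rejection, 508 per arm |
|---|---|---|---|---|
| First run | Chi-square on observed final status | 3.0–3.1 points | 7.4% | 14.3% |
| Independent second run | Chi-square on observed final status | 2.9 points | 6.8% | 14.7% |
| Independent second run | Mixed logistic model, all reports | centred on zero | 4.0% | 4.7% |

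The second run also let dropout depend on the last report in one arm. The nominal level is 5%. If the dropout rule is the same in both arms, the completer rates shift equally and the null comparison is unbiased.

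**4. Does scoring all lost participants as nonadherent repair it?** Assume true adherence 40% in both arms, 20% loss in each, loss unrelated to adherence in control, and intervention dropouts adherent at half the completers' rate.

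- Intervention completers: 0.8p + 0.2 × 0.5p = 0.40, so p = 0.40 / 0.9 = 44.4%, against 40% in control.
- Chi-square on completers, 120 per arm: SE = √[(0.444 × 0.556 + 0.40 × 0.60) / 120] = 0.064. Bias/SE = 0.044 / 0.064 = 0.70. Two-sided type I error, P(|Z + 0.70| > 1.96), is 10.7%.
- Lost scored nonadherent, 150 per arm: 0.8 × 44.4% = 35.6% against 0.8 × 40% = 32%. SE = √[(0.356 × 0.644 + 0.32 × 0.68) / 150] = 0.055. Bias/SE = 0.65. Type I error is 10.0%.

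Scoring everyone lost as nonadherent barely changes the result. It applies one rule to both arms when the problem is a difference between the arms.

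**The case against.** The strongest reply is that the article never says lost participants are excluded. A chi-square can be run on imputed or recoded data, and the rule for missing values may stand in an analysis plan that is not shown. That is right. A reader might infer that the plan drops these participants and so flatly contradicts its own intention-to-treat statement, but the text does not support this. The intention-to-treat sentence concerns adherence to assigned treatment and does not address missing outcomes, so there is a tension and no more. What stands is the choice of method: even with an imputation rule, the named test reads one status per person from a longitudinal binary outcome.

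Other points on that side also have weight:

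- The article does not expressly equate the primary outcome with the adherent/nonadherent status. STEPS data and pedometer counts are collected too. The reading is still the natural one, because no other passage gives a yes/no compliance measure for both diet and activity. The step count covers activity only and has no stated compliance threshold.
- No visit is tied to the chi-square. Use of the final visit is inferred from the outcomes being set at the end of the trial.
- The 20% is stated for the T2DM sample size. It is the only attrition figure for the same people and visits.
- A reader might infer a severe false-positive rate. If every intervention dropout is nonadherent while control dropout is unrelated to adherence, the rates are 40 / 0.8 = 50% against 40%, and type I error is about 35% at 120 per arm. Nothing in the document supports that asymmetry. Equal loss with the same dropout-to-completer ratio in both arms gives no bias. The proposed model is not shown to remove bias in that scenario either.

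**Conclusion.** The concern holds as a point about method. If the behaviour outcome is the self-reported binary status, the one between-arm test named for it is a weak choice. On observed final status it would use about 240 of 300 people and no earlier report.

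The likely harm is modest: about 3 points of false difference, with type I error near 7% at 150 per arm and 14–15% at 508 per arm. Those sizes rest on the assumption that dropout depends on earlier reported adherence in one arm and not in the other. Lack of blinding makes this plausible, but no passage states it. The change is worth making because a better analysis can be had from data already planned. The plan's T2DM analysis is not affected by this point.

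**What to change.** - **Primary comparison.** For the adherent/nonadherent outcomes, specify a mixed-effects logistic model using every 6-monthly report. Include arm, visit, arm-by-visit and baseline behaviour, and read the arm contrast at the final visit. Keep the chi-square as a descriptive table.
- **Sensitivity analysis.** The model corrects only loss that observed reports explain. Add an analysis that varies the assumed adherence of lost participants separately in each arm and shows where the conclusion changes. A single rule scoring all lost participants as nonadherent is not enough.
- **Wording.** State that the behaviour outcome is this status, if that is intended, and how a missing status enters the all-participants analysis.

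The cost is analysis wording and a little programming, with no new data or participants. The downside is that a model-based odds ratio is slightly harder to present than a two-by-two table.

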#### Physical measurements

At the baseline visit, all recruited participants’ weight, height, waist circumference, and blood pressure from the left arm will be measured in a sitting position, and the mean of two readings will be considered. Blood tests for HbA1c and lipid profiles will be performed by qualified laboratory personnel. Glycated hemoglobin (HbA1c) and fasting lipid profiles will be measured for all participants at baseline and at every 6-month follow-up visit.

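### Outside the Cox model the plan names only unadjusted between-group tests, although baseline values are collected; for continuous outcomes this gives up precision, without causing bias.

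*Protocol article*

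**What the plan says.** The Data analysis plan of the protocol article lists its tests by type of variable. For numeric variables: "The t-test or Mann-Whitney test will be used to compare numeric variables". For categorical variables: "The chi-square statistical test will be applied for categorical variables to assess the association between them". It then gives repeated measures analysis of "variances or Friedman’s test will be used to evaluate repeated measures over the follow-up period". Covariates appear once, for hazard ratios: "the adjustment of known confounders will be adopted in the Cox regression model".

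The baseline values exist. Under Physical measurements: "Glycated hemoglobin (HbA1c) and fasting lipid profiles will be measured for all participants at baseline and at every 6-month follow-up visit", and at the baseline visit "weight, height, waist circumference, and blood pressure from the left arm will be measured in a sitting position". Under Assessment of interventions: "All participants will complete the WHO STEPS instrument version 3.1 at the baseline visit and during each follow-up visit"; that instrument covers diet and physical activity.

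The outcomes concerned are the behavioural part of the primary outcome ("Adoption of healthy lifestyle behaviors including healthy eating and physical activity practices complying with WHO recommendations"), HbA1c as a level, and the secondary outcomes on LDL-C, blood pressure, weight, activity and fruit and vegetable servings. Diabetes incidence has its own log-rank and Cox analysis and is outside this point.

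**The concern.** A two-sample test on follow-up values leaves in the error term all the between-person variation that the baseline value could explain. People who start heavier, or with higher LDL-C, tend to stay so, and an unadjusted test treats that persistence as noise. The standard error is then larger than it need be for the same participants.

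It matters here because the Sample size calculation rests on diabetes hazard alone. No power is stated for the behavioural outcome or the cardiometabolic outcomes, so their precision depends on the recruited number and on how they are analysed. Only the second can still be improved by a change of wording.

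**Working it through.** **The plan's own figure.** The only sample size is for diabetes incidence: 128 per group, 256 in total. With hazards 0.10 and 0.07 (mean 0.085), two-sided α = 0.05, 80% power and every participant followed to the event, the exponential-hazard formula gives

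n = [1.960 × √(2 × 0.085²) + 0.842 × √(0.10² + 0.07²)]² / 0.03² = 127.2 per arm, so 128.

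The figure reproduces, but it says nothing about the power for the outcomes discussed here.

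**Inputs.** From the Sample size calculation: α = 0.05 (taken as two-sided), 80% power as the reference level, 300 participants less 20% loss = 240, or 120 per arm. Assumed: ρ, and equal variance at baseline and follow-up. The documents give neither a standard deviation nor a correlation.

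**Reference effect.** The standardised difference that an unadjusted comparison detects with 80% power at 120 per arm is

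d = (1.960 + 0.842) × √(2/120) = 0.362.

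This d is solved for, not taken from the protocol. Because it is fixed to give 80%, the powers below do not depend on the number per arm.

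**Variance factors, relative to comparing follow-up values.**
- Linear model with baseline covariate (ANCOVA): 1 − ρ².
- Change score: 2(1 − ρ).
- Difference: 2(1 − ρ) − (1 − ρ²) = (1 − ρ)², never negative. ANCOVA is therefore at least as precise as change scores at every ρ.

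**Power** = Φ(2.802/√factor − 1.960). At ρ = 0.5 with ANCOVA: 2.802/√0.75 = 3.235, and Φ(1.275) = 0.899.

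| ρ (assumed) | 1 − ρ² | Follow-up values | Change score | ANCOVA | Unadjusted N matching 300 adjusted: 300/(1 − ρ²) |
|---|---|---|---|---|---|
| 0.3 | 0.91 | 80% | 65.8% | 83.6% | 330 |
| 0.5 | 0.75 | 80% | 80.0% | 89.9% | 400 |
| 0.6 | 0.64 | 80% | 87.9% | 93.8% | 469 |
| 0.7 | 0.51 | 80% | 95.1% | 97.5% | 588 |
| 0.8 | 0.36 | 80% | 99.3% | 99.7% | 833 |

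**Does the repeated-measures sentence already deal with this?** Friedman's test has no between-arm factor. The repeated measures ANOVA is given neither an arm term nor a baseline covariate. Suppose it had an arm term and treated baseline as one of seven time levels, with six follow-ups, equal correlation ρ between visits and a constant effect after baseline. The variances relative to a single measurement, for the same effect, are:

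| Contrast | Formula | ρ = 0.5 | ρ = 0.7 |
|---|---|---|---|
| Arm main effect, baseline included | [(1 + 6ρ)/7]/(6/7)² | 0.778 | 1.011 |
| Mean of follow-ups, unadjusted | (1 + 5ρ)/6 | 0.583 | 0.750 |
| Mean of follow-ups minus baseline (arm by time) | (1 + 5ρ)/6 + 1 − 2ρ | 0.583 | 0.350 |
| Mean of follow-ups, baseline as covariate | (1 + 5ρ)/6 − ρ² | 0.333 | 0.260 |

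The main effect is diluted, and the arm-by-time contrast is a change-score comparison. The baseline covariate is better than both.

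**Where the gain will be smaller.** Exercise above 50 min/week is an exclusion, so baseline activity has a narrow range and lies well below the 150 min/week at which adherence begins. The HbA1c range is narrowed in part by the 5.7–6.4% definition of prediabetes. None of the powers above is for a binary outcome.

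**The case against.** The sentence on numeric variables is a general list in a condensed article. It names no outcome, visit or arm, and does not say whether follow-up values or changes are compared. Several outcomes are worded as changes (HbA1c, blood pressure, weight), and a covariate list may stand in an analysis plan that is not shown. All of this is fair. A reader might infer that the plan commits each of these outcomes to a single-visit t-test on follow-up values; the text does not say so. What remains is that the article itself names the tests and itself confines covariate adjustment to the Cox model.

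A reader might also infer that analysing change recovers nothing. That holds only at ρ = 0.5, where change and follow-up values tie. At ρ = 0.7 change scores recover about 15 of the 17.5 points, and high correlations are plausible for weight and lipids. Below 0.5 change scores do worse than follow-up values.

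A third inference would be that the results are biased, or exposed to chance imbalance because allocation is unstratified. The named tests control type I error under randomisation, and their standard errors already allow for chance imbalance. The Randomization and blinding section is silent on stratification, which does not establish that there is none.

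Finally, the behavioural outcome is analysed as adherent or nonadherent, so the continuous-outcome powers cannot be carried over to it. That objection stands in full.

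**Conclusion.** The point holds as one of efficiency. Outside the Cox model the plan names no analysis that uses the participant's own baseline value as a covariate, although that value is collected.

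For continuous outcomes compared on follow-up values, adjustment would lift 80% power to about 84%, 90% or 97.5% at ρ = 0.3, 0.5 or 0.7. Against change scores the advantage is 10 points at ρ = 0.5 and about 2.4 points at 0.7. These figures rest on an assumed ρ, equal variances and an effect solved to give 80% power. A reader might take 80% to 90% as a measured shortfall of this trial; it is an illustration, because the protocol states no power for these outcomes.

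The gain is likely to be largest for weight, lipids, blood pressure and servings, small for activity, possibly reduced for HbA1c, and unquantified for binary adherence. The named tests are valid, so this is a worthwhile improvement and not the correction of an error.

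**What to change.** In the Data analysis plan:
- For continuous outcomes (HbA1c, LDL-C, weight, blood pressure, servings), name as the between-arm analysis a linear model of the follow-up value on arm and the participant's own baseline value, transformed or rank-based if skewed. Report the arm difference with its 95% CI.
- For diet and activity adherence (adherent/nonadherent), name a regression on arm and the baseline STEPS value. Report a standardised risk difference with its 95% CI.
- Keep the t-test, Mann-Whitney and chi-square tests as supportive.

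Settle this before any unblinded comparison, so that the choice of adjustment cannot depend on the results. The cost is a change of wording, slightly more analysis work and a simple rule for a missing baseline value, such as mean imputation of the covariate. Missing values should be rare, since baseline is measured in everyone. No new data or visits are needed.
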